## Abstract

**Background:**

Lung cancer is the leading cause of cancer death in North America and Western Europe. Patients with lung cancer in general have reduced physical capacity, functional capacity, poor quality of life and increased levels of anxiety and depression. Intervention studies indicate that physical training can address these issues. However, there is a lack of decisive evidence regarding the effect of physical exercise in patients with advanced lung cancer. The aim of this study is to evaluate the effects of a twelve weeks, twice weekly program consisting of: supervised, structured training in a group of advanced lung cancer patients (cardiovascular and strength training, relaxation).

**Methods/Design:**

A randomized controlled trial will test the effects of the exercise intervention in 216 patients with advanced lung cancer (non-small cell lung cancer (NSCLC) stage IIIb - IV and small cell lung cancer (SCLC) extensive disease (ED)). Primary outcome is maximal oxygen uptake (VO_2_peak). Secondary outcomes are muscle strength (1RM), functional capacity (6MWD), lung capacity (Fev1) and patient reported outcome (including anxiety, depression (HADS) and quality of life (HRQOL)).

**Discussion:**

The present randomized controlled study will provide data on the effectiveness of a supervised exercise intervention in patients receiving systemic therapy for advanced lung cancer. It is hoped that the intervention can improve physical capacity and functional level, during rehabilitation of cancer patients with complex symptom burden and help them to maintain independent function for as long as possible.

**Trial registration:**

http://ClinicalTrials.gov, NCT01881906

## Background

Lung cancer is the leading cause of cancer death in North America and Western Europe [1]. In Denmark, the relative survival 1, 3 and 5 years after diagnosis of lung cancer is 32%, 13% and 10%, respectively. The best prognosis is achieved for patients who have lung cancer at an early stage (Non-small Cell Lung Cancer (NSCLC) stage I-IIIa and Small Cell Lung Cancer (SCLC) limited disease (LD)) and are receiving treatment with curative intent. For patients with advanced lung cancer (NSCLC IIIb-IV SCLC ED), the median survival after diagnosis is 10–13 months [2]. Despite improved treatment methods with surgery, chemotherapy, biological therapy and radiotherapy and more focus on supportive therapy, survival has not changed significantly over the last 10 years [3].

Patients with lung cancer receiving chemotherapy often experience a range of treatment- and disease-related symptoms such as dyspnea, cough, pain, decreased appetite, decreased functional capacity, and fatigue [4]. A comparison of quality of life (HRQOL) in treated lung cancer patients with other treated cancer patients indicates that patients with lung cancer in particular are suffering from several physical and psychosocial problems [5-7]. A Danish study highlighted physical, psychological and social problems among cancer patients with a broad spectrum of diagnoses. The results showed that lung cancer patients had more symptoms and side effects, increased anxiety and depression levels and impaired HRQOL compared to patients with 10 other cancer diagnoses [8]. Patients with metastatic, incurable tumors, such as lung and pancreatic cancer, reported the heaviest symptom and side effect burden compared with other cancer diagnoses [9].

It is well documented that physical activity can relieve symptoms and side effects in selected groups of cancer patients, including fatigue, cachexia and depression [10-15]. The benefits of physical activity for cancer patients have been described in several studies [16-21]. The majority of these studies include patients with breast cancer, prostate cancer and haematological malignancies. These studies have primarily measured the physical, functional capacity and HRQOL and predominantly included patient groups with relatively low disease burden.

In 2006 [22], our group demonstrated in a non-randomized study that 6 weeks of intervention with physical training (4× weekly) was beneficial to cancer patients with different diagnoses, both in early and in advanced stages. Patients increased their muscle strength (1RM) by 41% and V0_2_max by 14.5%. The effect of this intervention was confirmed in a randomized controlled study from 2009 [23], where in addition to an increase in muscle strength and V0_2_max, patients also reported a clinical significant reduction in fatigue. The study included 269 patients with different diagnoses, with few patients having lung cancer (n = 10). Analyses showed that lung cancer patients receiving chemotherapy indicated the same (percentage) physical progress as other cancer patients. However, lung cancer patients had significantly lower VO_2_max at baseline compared to other diagnostic groups (lung _VO2_max baseline = 1.15 L/min vs. other diagnoses baseline 2.27 L/min). Moreover, the lung cancer patients indicated that the exercise intensity (4 times per week) was too strenuous.

The existing knowledge about the effects of physical activity for lung cancer patients with advanced disease is sparse. The majority [24-28] of the studies that have tested aerobic training have been performed on lung cancer patients in an early stage of disease (NSCLC I-II LD SCLC) who did not receive chemotherapy and/or radiotherapy. The studies showed significant successes with regard to HRQOL and physical function (6 MWD) and physical capacity (VO_2_peak and 1RM) but have included relatively few patients (N = 10–23). Three studies have included patients with advanced inoperable lung cancer receiving chemotherapy [29-31]. Temel et al. [30] studied the effect of an eight-week (2 × weekly) training (fitness and strength) on 25 patients with lung cancer (NSCLC stage IIIb - IV), of which 18 patients received chemotherapy. The results showed no significant improvement in quality of life, anxiety or depression as measured by Functional Assessment of Cancer Therapy - Lung (FACT-L) and Hospital Anxiety and Depression scale (HAD). The physiological results showed a significant increase in strength of a single muscle group. There was no significant progress in the functional walk test (6MWD). Other studies have shown that physical exercise and relaxation techniques can relieve side effects and symptoms in cancer patients with advanced disease receiving chemotherapy [23,32,33].

In a pilot study from 2011 [29], our group showed that advanced (inoperable) lung cancer patients (NSCLC IIIb-IV SCLC ED) in chemotherapy could increase their exercise capacity (fitness, strength), functional capacity (6MWD) and emotional well-being (FACT-L) in a physical intervention (supervised and home exercises) two times weekly for 6 weeks. Patients reported no change in HRQOL. This study also showed that this intervention was feasible and safe for inoperable lung cancer patients receiving chemotherapy. Home training in addition to the supervised training was not feasible due to lack of compliance [34].

According to published data, patients with lung cancer in general have reduced physical capacity, functional capacity, poor quality of life and increased levels of anxiety and depression. Intervention studies indicate that physical training can address these issues in lung cancer patients with low stage (I-IIIa). We and others have shown that physical exercise for lung cancer patients with advanced stage (IIIb-IV) is safe and feasible (29;34). However, there is a lack of decisive evidence regarding the effects of physical exercise.

The aim of this study is to evaluate the effect of twelve weeks of a physical and psycho-social program consisting of: supervised, structured training in a group of advanced lung cancer patients (cardio and strength training, relaxation training) twice weekly. Primary outcome is (VO_2_peak). Our hypotheses are that patients who undergo this intervention will increase maximal oxygen uptake (VO_2_peak), strength (1RM), functional capacity (6MWD) and quality of life (HRQOL) and reduce the level of anxiety and depression.

## Methods/Design

This randomized controlled trial is being led by the University Hospitals Centre for Health Research at the University Hospital of Copenhagen, Denmark. The study is supported by grants from The Center for Integrated Rehabilitation of Cancer patients (CIRE), a center established and supported by The Danish Cancer Society and The Novo Nordisk Foundation. The study is prospectively registered with the Clinicaltrials.cov; registration number NCT01881906. Ethics approval has been obtained from the scientific Ethics Review Committee for the Capital Region of Denmark (J. HA-2008-06). The study is approved by the Danish Data protection agency Inspectorate (J. 2008-41-2279). The Intervention components will be tested on 216 patients with lung cancer (NSCLC stage IIIb - IV and SCLC ED) recruited from the lung cancer section at the dept. of oncology Copenhagen University Hospital, Rigshospitalet. All included patients will provide signed informed consent prior to initiation of any study procedures.

### Procedures

Eligible patients >18 years with a WHO performance status 0–2 with stage IIIb-IV NSCLC and SCLC-ED who are undergoing chemotherapy at the Department of Oncology are randomized to standard care or a 12 week physical and psycho-social intervention (Figure 1). Randomization is stratified for sex and lung cancer type (NSCLC or SCLC). Randomization is performed by the Copenhagen Trial Unit (CTU). Exclusion criteria are: brain or bone metastases; prolonged bone marrow suppression; anti-coagulant treatment; symptomatic heart disease, including congestive heart failure, arrhythmia or myocardial infarction diagnosed within the last three months; and inability to provide informed consent.

**Figure 1 F1:**
[figure not shown]
Study flowchart.

### Control – usual care

Patients who are randomized to the control group receive no training but are offered participation in the supervised training after completion of antineoplastic treatment, starting no earlier than twelve weeks after initiation of chemotherapy. Patients in early 2nd line treatment (“switch maintenance”) will be offered training after 12 weeks, although they have not necessarily completed chemotherapy.

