### Intervention

The supervised training is carried out in groups of 12–16 patients and each session has a duration of 1.5 hours, is administered twice weekly and is supervised by a research physiotherapist. The training comprises warm up exercises, strength and fitness training as well as stretching. Warm up exercises consist of 10 minutes of light, stationery cycling, adjusted to 60-90% of the patient’s maximum HR. Strength training is carried out using 6 machines (Technogym: Leg press, chest press, lateral machine, leg extension, abdominal crunch, and lower back). The practical aim of strength training is to complete 3 series of 5–8 sets, with 70-90% of 1RM. The exercises are specifically selected to involve the largest possible number of muscle groups in the least number of exercises. To ensure progression in strength training, each patient is instructed in carrying out the 1RM test using each of the above-mentioned strength training machines once every second week, after which their program will be adjusted. Cardiovascular training is carried out as interval training on stationery bikes. Intensity is equivalent to 85-95% of each patient’s maximum HR and lasted approximately 10–15 minutes. After the training session, 5–10 minutes are dedicated to stretching the large muscle groups in order to increase agility. Following each training session, progressive relaxation of 15–20 minutes is performed.

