### Study endpoints and assessments

Outcomes will be assessed at baseline (prior to randomization), 12 weeks and 12 months (Table 1). Baseline assessments involve a medical history; disease and treatment status is recorded from medical records and subjects will complete patient reported outcome (PRO) questionnaires, aerobic capacity (VO_2_peak (Cardio-Pulmonary Exercise Test (C-PET)), muscle strength (1RM), Functional capacity (6 Minute Walk Test (6MWT)).

**Table 1 T1:** Assessments

*Physical capacity:*	Baseline
VO_2_*peak*	12 weeks, and 12 months from the start of the intervention
*Muscle strength:*	Baseline
1RM	12 weeks, and 12 months from the start of the intervention
*Body Composition:*	Baseline
weight / height, blood pressure, resting heart rate	12 weeks, and 12 months from the start of the intervention
*Lung function*	Baseline
Fev1	12 weeks, and 12 months from the start of the intervention
*Socio-demographic*	Baseline
self-developed	12 weeks, and 12 months from the start of the intervention
*Social support and network*	Baseline
MSPSS	12 weeks, and 12 months from the start of the intervention
*Health related quality of life*	Baseline
EORTC QLQ-C30-LC13, FACT-L HADS, SF36	12 weeks, and 12 months from the start of the intervention

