### Primary and secondary endpoints

The primary endpoint will be VO_2_ peak, as assessed with an aerobic capacity incremental C-PET on a cycle ergometer (Monark, ergomedic 839E). The C-PET is carried out by a physiotherapist who is blinded to the patient’s study group allocation. The test consists of a warm-up phase 2–4 minutes of cycling at a sub maximal load (10–50 watts). After the warm-up period the load increases after a short break (<2 minutes) by 5–10 watts every minute, until exhaustion or a possible symptom limitation (e.g. dizziness, sudden pain, vomiting sensation). Expired gases are analyzed continuously by a metabolic breath-by-breath analysis and calculated as an average over 15 seconds using the Oxycon Pro, Jaeger measurement system. During the C-PET, oxyhemoglobin saturation and heart rate is continuously monitored. After each test, maximum ventilation, respiratory exchange ratio (RER), possibly plateau in the increase in VO2, self-perceived exertion perception in the final seconds of the C-PET and maximal heart rate (Polar Team System 2, Polar, Finland) are recorded. Rating of perceived exertion is evaluated at the end of each workload using the modified Borg Scale. The primary outcome will be a comparison of VO_2_ peak in the intervention and control arms at the conclusion of the intervention (i.e. at the 12-week assessment).

Muscle strength is measured by the one repetition maximum (1RM) [36] test using a Technogym™ that includes a leg press (lower extremity), chest press (pectoral muscles), lateral machine (latissimus dorsi), leg extension (quadriceps femoris), abdominal crunch (rectus abdominis) and lower back press (erector spinae). The 1RM test is the golden standard and has been found to be a reliable assessment to measure upper and lower extremity strength [36].

Functional capacity is measured by a 6 MWD test. The test is carried out over a pre-measured distance of 28 meters, in compliance with the American Thoracic Society (ATS) statement [37]. The 6MWD test has demonstrated good reliability and validity in COPD patients who are similar to patients with lung cancer with regard to disease patophysiology and symptomatology [38].

Lung capacity Forced Expiratory Volume in 1 second (FEV1) is measured using a standard spirometry in a standing position with the use of the Oxycon Pro, Jaeger measurement system.

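### Two 12-week limits run from different dates, so some controls who finish treatment early or are on switch maintenance can be trained before their primary exercise test

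*Protocol article*

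**What the plan says.** Four sections of the protocol article bear on the point.

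- **Control – usual care.** Controls get no training at first but "are offered participation in the supervised training after completion of antineoplastic treatment", with a floor: "starting no earlier than twelve weeks after initiation of chemotherapy". Both conditions must be met. Patients on early second-line treatment (switch maintenance) are handled separately: they "will be offered training after 12 weeks, although they have not necessarily completed chemotherapy". The date from which those 12 weeks run is not given.
- **Procedures.** The randomised population is patients "who are undergoing chemotherapy at the Department of Oncology are randomized to standard care or a 12 week physical and psycho-social intervention". No maximum time since the first cycle is set.
- **Study endpoints and assessments.** The text says "Outcomes will be assessed at baseline (prior to randomization), 12 weeks and 12 months". Table 1 gives the follow-up times as "12 weeks, and 12 months from the start of the intervention".
- **Primary and secondary endpoints.** The primary comparison of VO2peak is made "at the conclusion of the intervention (i.e. at the 12-week assessment").

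No section says that a control patient's 12-week test must come before that patient's first training session.

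**The concern.** The control arm's access to training is counted from chemotherapy, while the primary test is counted from the intervention. Chemotherapy has begun by the time of randomisation, so the first limit can expire before the test is due. A control who has completed treatment by then may join the same programme that the trial is testing. A switch-maintenance control may do so without having completed treatment, if the unstated 12 weeks run from chemotherapy start.

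A second gap adds to this. Start of the intervention is not defined for someone who receives none, so the due date of a control's 12-week test is open to interpretation.

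The primary contrast is at stake. The sample size assumes that controls lose 0.5 ml/kg/min, which presupposes that they are untrained. If training works, controls trained before the test move toward the intervention arm and the difference shrinks. The analysis cannot undo this, and cannot even detect it unless the dates of control sessions are recorded.

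**Working it through.** **1. The plan's own figure.** Inputs from Sample size: gain of 0.85 ml/kg/min with training, SD 2.48, control change −0.5, significance level 0.05, power 80%.

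- Difference: 0.85 − (−0.5) = 1.35.
- Standardised difference: 1.35 / 2.48 = 0.544.
- A two-sided two-sample t-test needs 53.95, so 54 per arm and 108 in all. Power at 54 per arm is 80.0%.
- With 50% drop-out: 108 / 0.5 = 216.

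The stated 108 and 216 reproduce, with no power to spare.

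**2. The possible overlap.** Let L be the weeks from first chemotherapy to the start of the intervention (for a control, the equivalent date).

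- Chemotherapy-based floor, on the study clock: week 12 − L.
- Primary test: week 12.
- Longest permitted training before the test: 12 − (12 − L) = L weeks. The training "is administered twice weekly and is supervised by a research physiotherapist", so this is 2L sessions.

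| L (assumed) | Earliest control training, study week | Overlap, weeks | Sessions |
|---|---|---|---|
| 0 | 12 | 0 | 0 |
| 1 | 11 | 1 | 2 |
| 3 | 9 | 3 | 6 |
| 6 | 6 | 6 | 12 |

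**3. Who can be exposed.**

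- A control still on treatment at the test, and not on switch maintenance: not exposed.
- A control who completes treatment before the test, with the floor already passed: can be exposed.
- A switch-maintenance control: can be exposed if the 12 weeks run from chemotherapy start; not exposed if they and the test both run from randomisation.

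**4. Effect on power.** The document gives neither the share of controls trained early (f) nor the weeks they train (k), so both are assumptions. Keep the plan's 1.35 difference as what 12 weeks of training produces, and let it accrue evenly.

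- Gain of a control trained for k weeks: k × (0.85 + 0.5) / 12 = 0.1125k.
- Diluted difference: 1.35 − f × 0.1125k.
- Power: two-sided t-test, 54 per arm, SD 2.48.

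| f | k | Gain per trained control | Diluted difference | Power |
|---|---|---|---|---|
| 0 | – | – | 1.35 | 80% |
| 10% | 2 | 0.225 | 1.35 − 0.0225 = 1.33 | 79% |
| 20% | 3 | 0.3375 | 1.35 − 0.0675 = 1.28 | 76% |
| 30% | 4 | 0.45 | 1.35 − 0.135 = 1.215 | 71% |
| 50% | 4 | 0.45 | 1.35 − 0.225 = 1.125 | 65% |

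**The case against.** The best defence is that the intent is plain. Controls are to receive no training, the primary comparison is tied to the end of the intervention, and the later offer reads as a courtesy after the study period. The article is condensed and its flowchart is not shown; visit windows and visit order may well be in the full protocol. Completion of treatment is a real condition that keeps many controls out until later. If patients are randomised and start at about their first cycle, L is near zero and so is the overlap. Any early training would also weaken a true effect rather than create a false one.

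Most of this stands, and it limits the point. It does not remove it, because the article does state both time limits and they do not agree. This is more than detail left to another document.

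Three stronger readings are tempting and are not supported:

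- *That any control may train 12 weeks after chemotherapy began, or that overlap always occurs.* The completion condition and the unknown lag rule this out. The text supports only that overlap can occur.
- *That intervention patients are tested later because they wait for a group to fill.* The Intervention section gives groups of 12–16 but does not say that a group starts together. Rolling entry fits equally well.
- *That the power loss is larger, since the pilot gained 0.85 in six weeks.* Crediting trained controls at that rate, while holding the intervention arm to 0.85 over 12 weeks, gives 73%, 65% and 53% for the last three scenarios. The two arms are then treated inconsistently. At the six-week rate the intervention arm would gain 1.70, the difference would be 1.70 + 0.5 = 2.20, and undiluted power would exceed 99%.

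**Conclusion.** The point holds in a limited form. The access rule permits some controls to be trained before their primary test: those who complete treatment early, and those on switch maintenance if their 12 weeks run from chemotherapy start. The maximum overlap equals the lag from first chemotherapy to the start of the intervention. The bias is toward no effect.

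The loss is small if few controls are involved (about one percentage point of power at 10% for 2 weeks) and material if many are (about 15 points at 50% for 4 weeks). These figures rest on an assumed share, an assumed duration and an even gain over 12 weeks. The number affected could be nil. The sample size itself is sound if no control trains before the test. This should be fixed, but it is not a fatal flaw.

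**What to change.** Reconcile Procedures, Control – usual care, Study endpoints and assessments (with Table 1) and Primary and secondary endpoints on one time origin that exists in both arms, such as the date of randomisation. In particular:

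- Time the 12-week and 12-month assessments from that origin in both arms.
- State the origin of the 12 weeks for switch-maintenance patients.
- State that a control's 12-week exercise test is done before that patient's first supervised study session.
- Record the date of any control's first session, so that early crossover can be identified and examined in a sensitivity analysis.

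The cost is a few sentences and one data field. The small downside is that some controls may be offered training slightly later. The sample size does not change.

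### The controls' training offer and the primary 12-week VO2peak test run on different clocks, so the text permits some controls to start training before their primary endpoint is measured

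*Protocol article*

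**What the plan says.** Four parts of the protocol article bear on this point.

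- **Control – usual care.** Controls get no training at first. Later they "are offered participation in the supervised training after completion of antineoplastic treatment". A time floor is added to that condition: "starting no earlier than twelve weeks after initiation of chemotherapy". Switch-maintenance patients (early second-line treatment) are handled separately: they "will be offered training after 12 weeks, although they have not necessarily completed chemotherapy". That sentence does not say from when its 12 weeks are counted.
- **Procedures.** Patients "who are undergoing chemotherapy at the Department of Oncology are randomized to standard care or a 12 week physical and psycho-social intervention". The article gives no figure for how long chemotherapy has been running at that point.
- **Study endpoints and assessments.** "Outcomes will be assessed at baseline (prior to randomization), 12 weeks and 12 months". Table 1 gives the origin of the follow-up times: "12 weeks, and 12 months from the start of the intervention".
- **Primary and secondary endpoints.** The primary comparison of VO2peak between arms is made "at the conclusion of the intervention (i.e. at the 12-week assessment").

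The Sample size section assumes that the trained arm gains 0.85 ml/kg/min (SD 2.48) and that the control arm loses 0.5.

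**The concern.** Both rules use twelve weeks, but they start counting from different events. The time floor on the controls' offer counts from the first chemotherapy. The primary test counts from the start of the intervention. Because patients are on chemotherapy when they are randomised, the first count cannot start later than the second and may start earlier. No sentence makes the offer wait until that patient's 12-week test has been done.

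A control who trains before the test has received part of the experimental programme inside the comparison window. That would pull the control mean towards the trained mean, for VO2peak and also for 1RM, 6MWD and the patient-reported outcomes. The planned t-test on change scores cannot recover what is lost. The design has no reserve for this, since the evaluable sample size gives almost exactly 80% power on the assumption that controls decline.

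**Working it through.** **1. Order of the two clocks.** Let L be the weeks from the start of chemotherapy to the start of the 12-week trial period. For a control, who has no intervention start of his or her own, I take the trial period to run in parallel with that of the training arm.

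- Earliest offer allowed by the time floor: trial week 12 − L.
- Primary test: trial week 12.
- Possible lead of the offer over the test: 12 − (12 − L) = L weeks.

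L is zero or more because patients are undergoing chemotherapy at randomisation. The article gives no value. With L = 0 the lead vanishes. With L = 3 the floor is passed at trial week 9.

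**2. Who could be affected.** The floor is only one of two conditions.

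- Controls outside switch maintenance: treatment must also be complete. The lead is usable only by a control whose treatment ends before that patient's 12-week test.
- Switch-maintenance controls: completion is not required. If their 12 weeks run from chemotherapy initiation, the lead is L weeks. If they run from the start of the trial period, there is no lead.

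**3. The plan's own figure.** Inputs from the Sample size section: difference 0.85 + 0.5 = 1.35 ml/kg/min, SD 2.48, significance level 0.05 (two-sided assumed, which reproduces the figure), power 80%.

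- The two-sample t-test needs 53.95, so 54 per arm and 108 in total, as stated.
- Noncentrality at 54 per arm: 1.35 / (2.48 × √(2/54)) = 1.35 / 0.477 = 2.83 on 106 degrees of freedom, giving power 80.0%.
- Drop-out: 108 / (1 − 0.5) = 216, as stated.

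**4. Illustrative dilution.** Assumptions that are not in the article: a fraction p of controls starts w weeks before the test, the benefit builds up linearly to 1.35 over 12 weeks, and the SD is unchanged.

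Diluted difference = 1.35 × (1 − p × w/12).

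| p | w | Difference | Power, 54 per arm |
|---|---|---|---|
| 0 | – | 1.35 | 80% |
| 10% | 1 | 1.35 × (1 − 0.10 × 1/12) = 1.34 | 79% |
| 10% | 3 | 1.35 × (1 − 0.10 × 3/12) = 1.32 | 78% |
| 25% | 3 | 1.35 × (1 − 0.25 × 3/12) = 1.27 | 75% |
| 50% | 3 | 1.35 × (1 − 0.50 × 3/12) = 1.18 | 69% |

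The speed of build-up matters. The earlier data cited for the sample size come from six weeks of training. If the full 1.35 were reached in six weeks, w/12 becomes w/6, and three weeks of early training gives 76% at p = 10% (difference 1.28) and 69% at p = 25% (difference 1.18).

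**The case against.** The strongest reply is that the text sets a floor, not an opening date. It allows any later start, nothing is triggered at week 12, and completion of antineoplastic treatment must also be met. The authors wrote a special sentence for patients who have not completed chemotherapy, which suggests that they saw completion as a binding condition for everyone else. The switch-maintenance sentence may count from the trial period, which would protect those patients. Enrolment may occur close to the first cycle, making L near zero. The flowchart (Figure 1) and the full protocol are not shown, and either could fix the order of events.

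Much of this stands. A reader might infer that the plan, followed as written, gives part of the control arm the programme inside the comparison window. The article does not support that: it fails to exclude early training but does not call for it. A reader might also infer a severe loss of power. Under the same linear 12-week model, 56% needs half of the controls to start six weeks early, and 29% needs all of them to do so. Nothing in the article supports such values, and the completion condition argues against the second.

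What does not fall away is the mismatch itself. The article does more than leave a detail to a fuller document: it states a rule and ties it to a different event from the one that times the primary endpoint. Completion limits how many controls could train early but does not exclude a control whose treatment ends before the test. The opening statement that controls receive no training does not settle the matter, because the offer in the same sentence is tied to treatment and not to the assessment.

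**Conclusion.** The point holds as a weakness in a stated rule. The article permits some controls to begin the supervised programme before their primary VO2peak test, and nothing shown prevents it. It does not establish that any control would do so.

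The direction of the effect is clear: early training that works would shrink the contrast towards no difference. The size is unknown, because neither the share of controls affected nor the lead time is given. For a three-week lead and linear benefit over 12 weeks, power is about 78%, 75% or 69% with 10%, 25% or 50% of controls affected, and somewhat lower if benefit builds up faster. With no early starters it remains 80%. These figures are illustrations, not estimates. The stated sample size itself reproduces and is not in question here.

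**What to change.** Reconcile Control – usual care with Study endpoints and assessments and with Primary and secondary endpoints, so that the training offer and the 12-week test use one time origin.

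- State that the offer opens to a control only after that patient's 12-week study assessments (VO2peak, 1RM, 6MWD and questionnaires) are done, and that this applies to switch-maintenance patients too.
- Record the date of each control's first supervised session, so that any start before the assessment can be counted and reported.

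The cost is a sentence or two of text and one recorded date per control. No extra tests or staff are needed. The drawback is that some controls wait slightly longer for the offer, by at most the lag between their chemotherapy start and the start of the trial period if the assessment is done on time.
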